### 2.6. Assessment Schedule

Each participant would experience three assessments to go through the whole procedures in this study. The first assessment is for enrollment and would be given when women is confirmed eligible for participation. The second assessment would be conducted after 18th week postpartum but not later than 24th week. The final assessment would be performed in one year after delivery (Figure 1).

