### 4.1. Sample Analysis

Sample size was calculated according to the improvement rate of MOS grade after 12-week training using PASS 2019 software. According to the preliminary experiment, the improvement rate of MOS in the CG was 20% and that of women in EG was 60% at 6 months postpartum. Group sample sizes of 106 in each group achieve 90.248% power to detect a difference between the group proportions of 0.4. The CG proportion is 0.2. The EG proportion is assumed to be 0.4 under the null hypothesis and 0.6 under the alternative hypothesis. The test statistic used is the one-sided Z test (unpooled). However, in considering 20% of the possible dropout, a total of 260 women will be randomized.

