### 4.2. Statistical Analysis

Data will be analyzed using SPSS version 26.0 (SPSS, Inc., Chicago, IL, USA) and the statistically significant difference will be identified if *p* < 0.05. Descriptive statistics including numbers and proportions, means and standard deviations, or medians (P25, P75) will be used. Group differences in the primary and secondary outcomes will mainly use chi-square and student’s t tests. For primary outcome, we will count the rate of pelvic muscle strength reaching grade 4 at 6 months postpartum between EG and CG by chi-square test or Fisher’s exact test as appropriate. Analysis of the primary and secondary outcomes will be based on an intention-to-treat basis in consideration of the drop-offs from the follow-ups and be conducted by the statistician at Peking University Clinical Research Institute. For comparison between groups of quantitative data, the analysis of variance or Wilcoxon rank sum test will be used according to the data distribution; chi square test or exact probability method is used for counting data (if chi square test is not applicable), Wilcoxon rank sum test or CMH test is used for grade data, and logistic regression analysis is used for correlation analysis. Repeated ANOVA will be used to assess within-patient correlation. and multivariable linear regression models if potential confounders were imbalanced.

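### Repeated ANOVA, the only longitudinal method named, keeps only women seen at all three visits, which sits badly with an intention-to-treat analysis promised because of drop-offs

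*Protocol article*

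**What the plan says.** Section 2.6 of the protocol article fixes three assessments: "Each participant would experience three assessments to go through the whole procedures in this study". They fall at enrolment, between the 18th and 24th week postpartum, and at one year. Table 2 collects nearly all examinations and questionnaires at all three.

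Section 4.1 allows for loss to follow-up: "in considering 20% of the possible dropout, a total of 260 women will be randomized". Section 2.3 adds that a woman who becomes pregnant during follow-up is recorded as a drop-off.

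Section 4.2 sets the analysis population: "Analysis of the primary and secondary outcomes will be based on an intention-to-treat basis in consideration of the drop-offs from the follow-ups". Later in the same paragraph comes the one sentence on repeated measurements: "Repeated ANOVA will be used to assess within-patient correlation". No outcome, contrast or rule for incomplete visits goes with it. The software is stated as well: "Data will be analyzed using SPSS version 26.0".

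The other outcomes have their own methods. For the primary outcome: "we will count the rate of pelvic muscle strength reaching grade 4 at 6 months postpartum between EG and CG by chi-square test", with Fisher's exact test as the alternative. For ordered grades: "Wilcoxon rank sum test or CMH test is used for grade data".

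**The concern.** Classical repeated-measures ANOVA, which is what the SPSS general linear model procedure fits, needs a complete set of visits for each subject. A woman with one visit missing is deleted altogether, including the visits she attended. The paragraph gives drop-offs as its reason for intention-to-treat, then names a longitudinal method that discards drop-offs.

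The pregnancy rule in Section 2.3 makes this concrete. A woman who completes the programme, attends the second assessment and then conceives before one year would contribute nothing to the repeated analysis, although her post-intervention measurements are valid.

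At stake are the time-course results for the repeated, mainly secondary and quantitative outcomes, such as ultrasound indicators, body composition, strength and questionnaire scores. These could rest on a selected subset. Only the experimental arm takes on two supervised sessions a week for 12 weeks, so the arms could lose different kinds of women. The documents give no figure for that.

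The stated purpose is a second, smaller fault. Repeated ANOVA does not assess within-patient correlation. It allows for it while testing time and group-by-time effects. Without a named outcome or contrast, the sentence does not say what will be reported.

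**Working it through.** **Inputs.** 260 randomised, 20% dropout, 106 per group, rates of 0.2 (control) and 0.6 (experimental), and 0.4 for the experimental arm under the null, all from Section 4.1. 1:1 allocation from Section 2.5. Three visits, two of them follow-ups, from Section 2.6.

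**The plan's own figure.** Section 4.1 states: "Group sample sizes of 106 in each group achieve 90.248% power to detect a difference between the group proportions of 0.4". With an unpooled Z test and a null difference of 0.4 − 0.2 = 0.2:

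- SE = √(0.2×0.8/106 + 0.6×0.4/106) = √(0.40/106) = 0.0614
- Power = Φ((0.4 − 0.2)/0.0614 − 1.960) = Φ(1.296) = 0.9025

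This reproduces 90.248% at a one-sided alpha of 0.025. That section gives no alpha; the value is inferred because it matches, whereas 0.05 would give 94.6%. For dropout, 212/0.8 = 265, close to the 260 planned. The calculation concerns the primary proportion test, which does not use repeated ANOVA. It serves here only to confirm the 260 and the 20%.

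**Women excluded by a complete-visits rule.** If 20% of 260 miss at least one visit, 260 × 0.20 = 52 are excluded and 208 remain, 104 per arm.

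**Women a mixed model would recover.** A baseline-adjusted model recovers only women with exactly one of the two follow-ups. The documents do not give that number, so the rows below are assumptions that show the range.

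| Assumed pattern | Complete | Excluded by ANOVA | Exactly one follow-up (recovered) | No follow-up (not recovered) |
|---|---|---|---|---|
| 20% lost before the second visit | 208 | 52 | 0 | 52 |
| 20% lost between second and third visits | 208 | 52 | 52 | 0 |
| 10% missing independently at each follow-up | 260×0.9×0.9 = 210.6 | 49.4 | 260×2×0.1×0.9 = 46.8 | 260×0.1×0.1 = 2.6 |
| 20% missing independently at each follow-up | 260×0.8×0.8 = 166.4 | 93.6 | 260×2×0.2×0.8 = 83.2 | 260×0.2×0.2 = 10.4 |

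With total loss held at 20%, the gain runs from 0 to 52 women, depending on when they leave. It is larger if 20% are missing at each follow-up.

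**The case against.** The strongest reply is that repeated ANOVA has a subsidiary role. Section 4.2 says that group differences in primary and secondary outcomes will mainly be tested with chi-square and t tests. Those can be done visit by visit and do not drop a woman for missing another visit. Intention-to-treat concerns analysis as randomised, and imputation before the ANOVA would reconcile the two. Such detail may sit in a full protocol or analysis plan that is not shown. All of this stands, and it limits the point to the repeated-measures analyses. It does not remove the point, because the fault is in the method the article names, not in a detail it leaves out.

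Stronger readings are tempting, but the documents do not support them:

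- *Repeated ANOVA is misapplied to ordinal grades.* Section 4.2 sends grade data to Wilcoxon or CMH and counts to chi-square or exact tests. No sentence applies repeated ANOVA to MOS, POP-Q stage or SUI. Only a conditional caution remains, since no longitudinal method for these outcomes is named.
- *The primary result is biased by this choice.* It is a single-time-point comparison of proportions. Changing the repeated-measures method would not alter it.
- *The treatment effect is diluted by averaging in baseline.* That would hold for a group main effect, which the plan never says it will report. The group-by-time interaction is the usual test and is not diluted in this way.
- *At least 52 women would be lost and could be recovered.* The 20% is a planning allowance, not a minimum, and it may include women with no follow-up at all.

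**Conclusion.** The point holds in a limited form. The only repeated-measures method named is, in its classical form, a complete-visits method with no outcome attached and a misdescribed purpose. It is in tension with an intention-to-treat promise made because of drop-offs. A reader might call this an outright contradiction, but that goes too far: analysis as randomised can coexist with ANOVA if missing visits are handled first.

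On the plan's own allowance, 52 of 260 women would be excluded if 20% missed a visit. The number recoverable lies between 0 and 52 under that allowance and is not given. This assumes that the classical procedure is meant and that nothing is imputed beforehand. The direction of any bias cannot be established from the documents. The primary analysis and its power are unaffected. The change is worth making because it is specific and nearly free.

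**What to change.** Replace the repeated ANOVA sentence in Section 4.2 as follows:

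1. For repeated quantitative outcomes, name the outcomes and use a likelihood-based mixed model with arm, visit and arm-by-visit terms, adjusted for the baseline value. Include every randomised woman with at least one follow-up, in her allocated arm. Report the arm contrast at each follow-up visit with its confidence interval.
2. If MOS, POP-Q stage or SUI is analysed over time, use GEE or a logistic or ordinal mixed model.
3. Describe the purpose as estimating the arm difference at each visit while allowing for within-patient correlation.

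SPSS 26 has these procedures and no new data are needed. The cost is revised wording and slightly more analysis work. The likelihood-based models assume that visits are missing at random given the observed data. They do not in general remove bias from dropout that depends on unobserved outcomes, and with baseline as a covariate they leave out women with no follow-up. Both limits should be stated.

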### 2.3. Exclusion Criteria

Participants will be excluded if they are: (1) confirmed by postpartum pelvic examination to be >grade 3 of pelvic floor muscle strength by Modified Oxford Scale (MOS); (2) ≥stage III for Pelvic Organ Prolapse Quantification (POP-Q); (3) symptomatically confirmed to have severe urinary incontinence (Women with more than one incontinent episode per day AND an important volume of urine loss [28] or urine leakage occurred in a quiet state were classified as having severe urinary incontinence); or (4) any limb dysfunction that unenabled women to take this training. A participant will be recorded as“ drop off from trial” if she becomes pregnant during the follow-ups.

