### 2.5. Randomization and Allocation Concealment

Eligible women would be randomized into two groups, the experimental group (EG) and the control group (CG), at a ratio of 1:1. A randomization list would be created by a statistician from Peking University for each center before the start of the research. Randomization would be performed using SAS 9.4 (SAS Institute, Cary, NC, USA). The randomization lists would be concealed until a woman is confirmed eligible for participation. Then, the research coordinator in the site would assign the eligible participant to EG or CG. With such a randomization, the numbers of participants in EG and CG are expected to be statistically balanced. Participants and the physiotherapists engaging in the intervention are not blind to the randomized assignment because it is not feasible to do. However, to minimize the risk of assessor’s unblinding, participants are blind to other’s assignments and encouraged not to discuss their treatment with the independent assessor in the informed consent procedures and at the time of each assessment. 

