## 4. Outcomes of the Study

The primary outcome will be the comparison of participants’ pelvic floor muscle strengths using MOS scale at the enrollment baseline and post intervention. The secondary outcomes will be: (1) the occurrence of SUI, (2) the change of the Pelvic floor ultrasound indicators, (3) change of the Pelvic Organ Prolapse Quantitation measured by callipers, (4) change of the pelvic sagittal rotation degree, and (5) the change of the overall body composition and strength. The list of data collection instruments and time of data collection is presented in Table 2 and Table 3.

The other secondary outcome measures involved in the Table 2 will be calculated and discussed separately.

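### The primary test makes no use of baseline MOS, and the only covariate adjustment named waits for observed imbalance: a loss of precision, not a bias

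*Protocol article*

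**What the plan says.** Section 4 frames the primary outcome as a "comparison of participants’ pelvic floor muscle strengths using MOS scale at the enrollment baseline and post intervention". Section 4.2 makes it binary and fixes the test: "we will count the rate of pelvic muscle strength reaching grade 4 at 6 months postpartum between EG and CG by chi-square test". The named alternative is Fisher's exact test. Neither has a term or stratum for the grade at entry.

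The same section closes with a sentence fragment offering "multivariable linear regression models if potential confounders were imbalanced". It does not say which outcome this serves. Logistic regression has another role: "logistic regression analysis is used for correlation analysis". For ordinal outcomes, "Wilcoxon rank sum test or CMH test is used for grade data".

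On entry grade, section 2.3 excludes women "confirmed by postpartum pelvic examination to be >grade 3 of pelvic floor muscle strength by Modified Oxford Scale (MOS"), so grades 0 to 3 may enter. The abstract instead requires less than grade 3. Section 2.5 describes 1:1 allocation and says "With such a randomization, the numbers of participants in EG and CG are expected to be statistically balanced", which concerns the numbers per group. Table 2 schedules MOS at the first visit in both groups.

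**The concern.** Success means reaching grade 4. Under section 2.3 a woman at grade 3 needs one step and a woman at grade 0 needs four; under the abstract's rule the range is two to four steps. Either way, entry grade is probably the strongest single predictor of success, and it is available for everyone. A two-by-two test leaves that information unused.

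The one adjustment rule makes the choice of model depend on the baseline table. That is a poor principle in a randomised trial. A covariate should be in the model because it predicts the outcome, not because it happened to differ between arms. Linear regression is also not the natural model for a binary or ordinal outcome, should the sentence be read as reaching those outcomes. If it is meant only for continuous outcomes, the article gives no adjusted analysis of the primary endpoint.

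At stake are the precision of the primary estimate and some avoidable analytic flexibility.

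**Working it through.** **1. Reproducing the stated power (section 4.1).** Inputs: CG 0.2; EG 0.6 under the alternative and 0.4 under the null, hence a margin of 0.2; 106 per group; one-sided unpooled Z test. Alpha is not stated; one-sided 0.025 reproduces the figure.
- Variance term: 0.2×0.8 + 0.6×0.4 = 0.40.
- Z = 0.2/√(0.40/106) = 3.256.
- Power = Φ(3.256 − 1.960) = 0.90248, the stated 90.248%.
- One-sided 0.05 would give 0.946, which does not match.

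**2. Adjustment against that margin.** If adjustment multiplies the variance of the risk difference by r, power = Φ(3.256/√r − 1.960). Simulations (4,000 trials per scenario) with 104 per arm (260×0.8/2), assumed baseline shares of 5-40% per grade and CG success of 2-40% rising with grade gave r = 0.885 to 0.936, a fall of about 6-12%.
- r = 0.936: Φ(3.365 − 1.960) = 0.920.
- r = 0.885: Φ(3.461 − 1.960) = 0.933.

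So 90.2% becomes about 92-93%, conditional on that variance reduction carrying over to the planned effect.

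**3. Adjustment when testing no difference.** Simulations with 106 per arm, 4,000 trials per scenario, two-sided 5%. Assumed baseline grades: 20/40/40% over three grades or 10/20/30/40% over four. Assumed odds ratio for success per grade: 2 or 4.

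| CG v EG | Chi-square | Logistic, baseline MOS always in | Adjust only if MOS differs at p<0.05 |
|---|---|---|---|
| 20% v 20% (type I error) | 4.9-5.3% | 4.4-5.1% | 4.6-5.1% |
| 20% v 35% (power) | 68-70% | 70-78% | 68-71% |
| 20% v 40% (power) | 89-90% | 90-95% | 89-91% |
| 20% v 60% (power) | about 100% | about 100% | about 100% |

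Scenario by scenario, always adjusting gains 1.2 to 8.6 points at 20% v 35% (68.3 to 69.6%, up to 69.7 to 78.3%). At 20% v 40% it gains 1.3 to 4.7 points. The imbalance rule fired in about 5-6% of trials and moved power by about one point at most.

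A linear model with robust standard errors held type I error at 5.1-5.4%.

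**4. Dependence on assumptions.** The same simulations give the standard deviation of the crude and the linearly adjusted risk difference at 20% v 60%. The squared ratios run from (0.0602/0.0614)² = 0.961 to (0.0556/0.0625)² = 0.791. In the formula of step 2 these give 91.3% to 95.5%. The 92-93% is therefore a middle figure, and the gain grows with the prognostic strength assumed.

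**The case against.** The strongest reply is that nothing here is invalid. Section 4.2 fixes one primary test, allocation is randomised 1:1, and the unadjusted comparison holds its 5% error rate. At the planned 20% v 60%, power against no difference is already about 100%. Entry is capped at or below grade 3, so reaching grade 4 is always an improvement. Most secondary outcomes are defined as changes and so already use their baseline. A condensed article may also leave covariate lists and stratification factors to a fuller document. All of this stands, and no fault is found here for the absence of such lists.

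Three stronger readings are tempting, and the document does not support them:
- **Linear regression will be applied to the binary primary endpoint.** The fragment names no outcome, and ultrasound, pelvic rotation and body composition are continuous outcomes for which it is suitable. Nor would a linear model necessarily fail on a binary outcome: with robust errors it kept about 5%, although the article mentions no robust errors.
- **The primary estimate depends on a look at the baseline tables.** It does not; the chi-square or Fisher test is fixed for it.
- **Type I error is inflated.** Freely choosing the better of the adjusted and unadjusted results gave 5.9-6.8% in simulation, but the article plans no such choice. The imbalance rule itself gave 4.6-5.1%.

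What the reply does not remove is that the stated primary method leaves a measured, probably strong predictor unused, and that the stated trigger is the wrong basis for adjustment.

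**Conclusion.** The point holds as a matter of efficiency and clean prespecification. The primary analysis is valid but less precise than the collected data allow, and the conditional adjustment rule recovers almost none of the loss.

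The gain from always adjusting is roughly 1 to 9 power points at effects of 15 to 20 percentage points. It is nil at 20% v 60% against no difference, and about 2 to 3 points against the 0.2 margin if the variance falls by 6-12%. These figures rest on assumed baseline grade distributions and assumed prognostic strength, since the article supplies neither. The premise that entry spans grades 0 to 3 follows section 2.3. Under the abstract's narrower rule the span is 0 to 2, which shortens the range but does not remove it. The planned sample size is unaffected.

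**What to change.** - **Trigger.** Delete the imbalance condition in section 4.2.
- **Primary outcome.** Prespecify one analysis that includes baseline MOS whatever the observed balance. One option is logistic regression on arm and baseline MOS, reported as a standardised risk difference with 95% CI; the other is CMH stratified by baseline grade. Keep the chi-square or Fisher test as supportive.
- **Sparse grades.** In the logistic model, enter grade as a linear score or pool sparse low grades. With a 5% share and 2% success, 104 women per arm give about 5 women and 0.1 expected successes in a CG cell, so a separate category for each grade could fail to converge.
- **Secondary outcomes.** State that linear models are for continuous outcomes and adjust each for its own baseline by ANCOVA. Analyse SUI by logistic regression with baseline SUI, because only severe incontinence is excluded and milder leakage may be present at entry.

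The cost is a few sentences and slightly more analysis work. No new data are needed, and N does not change.

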Pregnancy and vaginal delivery have independently been proved to be the risk factors for the development of severe urinary incontinent (SUI) as they could obviously weaken the pelvic floor muscle (PFM) strength. However, it was hard to evaluate patients’ muscle strength objectively; therefore, it was hard to validate whether a measure could be effective to have the weakened pelvic floor muscles be recovered before Modified Oxford scale (MOS) for muscle strength was published [3]. MOS provides quantitative scales for muscle strength, and it is simple and easy to apply clinically. It is becoming widely accepted method for pelvic floor muscle strength assessment since it was published. Literately and clinically, MOS 4 and 5 is identified as having “good” or “strong” muscle contraction which represents a normal condition of the pelvic floor muscles; relevantly MOS ≤3 indicates a weak contraction or no contraction being felt [4]. Some studies suggested that pelvic floor muscle strength be correlated with the incidence of pelvic organ prolapse (POP). Thus, Pelvic Organ Prolapse Quantification (POP-Q) was developed for evaluation of the pelvic floor muscle [5]. Borello-France et al. [6] used POP-Q to evaluated women’s pelvic floor muscle in their studies and argued that women with stage II of prolapse were better than those with stage III or IV in elevating their pelvic floor, and also would be easier to get benefit from PFM training than those over stage III. Scientific evidence showed that 10–20% of patients who were not intervened for the clinically confirmed POP got progressed in term of POP-Q scoring in 2-year follow-up [7,8], so early prevention or treatment should have high priority. The incidence rate of POP is higher in middle aged and elderly women. PFM training is recommended to women postpartum for it reduces the incidence of PFD during 6–12 months postpartum [9] and should possibly reducing the incidence of diseases from muscle dysfunction related to the anatomical changes with aging [10]. A program of supervised PFM training was recommended as a first option for women with symptomatic POP-Q stage I or stage II [11]. MOS and POP-Q can be the objective indicators be used to validate the effectiveness of any measure in improving PFM.

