## 3. Data Collection and Management

Demographic data, including the age, height, weight, body mass index (BMI), prenatal maximum weight, physical activity during pre-pregnancy and pregnancy, and background data including the working position, smoking, alcohol consumption, urine leakage, asthma, constipation, family history of PFD, delivery history of pregnancy, weight gain during pregnancy, and fetal weight, would be collected at the enrollment visit of the study; while the following questionnaires would be filled by all participants at baseline and at all follow-up visits: (1)The International Physical Activity Questionnaire Score-Short Form (IPAQ-SF), which were recommended as a cost-effective method to assess physical activity by nine questions recording the activity of four levels of intensities in short forms: vigorous-intensity, moderate-intensity, walking, and sitting [31];(2)The Pelvic Floor Distress Inventory Questionnaire-20 (PFDI-20) and Pelvic Floor Impact Questionnaire-7 (PFIQ-7), which were designed to comprehensively evaluate to what extent the lower urinary tract, lower gastrointestinal tract, and pelvic organ prolapse symptoms affect the quality of life of women who suffer from PFD [32];(3)The Female Sexual Function Index (FSFI-6) [33], a common tool that has been validated for clinical use for evaluating female sexual function in six terms [34,35];(4)The Pittsburgh Sleep Quality Index (PSQI), which was developed in 1989 and accepted as the most common measure of sleep quality [36].

Baseline demographic data, IPAQ-SF, PFDI-20, PFIQ-7, FSFI-6, and PSQI were integrated into a WeChat mini program and can be filled by the Participants themselves by scanning a QR code on WeChat, a social App that is commonly used by the public in China. The body mass index (BMI) among the demographic data and all the scores or grades for all the questionnaires can be automatically come out by the configured formulas in the WeChat mini program. 

Following the questionnaires in each of the visits would be the physical examination including PFM strength evaluation by Modified Oxford Grading (MOS) [3], pelvic organ prolapse quantitation (POP-Q) stage [5], vaginal relaxtity, symptomatic SUI detection and grading, pelvic floor surface electromyography (sEMG) based on Glazer protocol [37], pelvic floor ultrasound examination, quantitative measurement of pelvic sagittal rotation degree by X-ray, and evaluation of the overall body composition and strength. 

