Pelvic floor surface electromyography (sEMG) would be tested based on Glazer protocol. The participants would be taught to contract the pelvic floor muscle correctly and will have one practice before testing.

SUI is defined by SUI symptoms or a positive result of the cough stress test. Before the cough stress test, participants are suggested to keep fully bladder. Positive result of the test is defined as involuntarily urinary leakage when asked to cough in the lithotomy position.

Pelvic floor ultrasound indicators, which include LAM thickness, diameter of the levator hiatus, and levator hiatus area, were measured using the proprietary software 4D View via transperineal ultrasound(GE Kretz Medizintechnik), a reproducible and reliable measurement of vaginal support [38].

The quantitative measurement of pelvic sagittal rotation degree on Spine X-ray (Definium7000, General Electric Company, Boston, MD, USA) was analyzed which includes the pelvic tilt angle, the sacral slope angle, the difference of sacral slope and pelvic tilt, the ratio of the pelvic tilt angle to the sacral slope angle, the ratio of the pelvic tilt angle to the pelvic incidence angle and sacral-femoral distance.

The change of the overall body composition would be analyzed through body composition analyzers (Inbody 770), and overall strength which would be measured through hand grip strength test and trunk endurance test. Body composition analyzers would analyze data regarding waist hip ratio, basal metabolic rate, body fat rate, etc. Hand grip strength would be measured by JAMAR Plus+ grip gauge. The measurement accuracy is 0.1 kg. The participants should not have visible hand defects. The grip gauge should be adjusted before measurement. When the participants hold the grip gauge, the second knuckle of the index finger should be at 90 degrees. At the same time, mark the best position of each hand on the grip meter. Before measurement, the participants should remove wrist jewelry to avoid injury. The left and right hand are measured alternately three times. Trunk endurance would be tested using the Plank test, Side bend test, and Biering–Sorensen Test [39]. All the participants were encouraged to keep the positions as long as possible. Time as recorded in seconds with a maximal length of 90 s.

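### Section 4.2 ties covariate adjustment to chance baseline imbalance and names only linear regression for it, although the primary rate and SUI are binary

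*Protocol article*

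**What the plan says.** Section 2.5 sets the design: "Eligible women would be randomized into two groups, the experimental group (EG) and the control group (CG), at a ratio of 1:1".

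Section 4.2 gives the primary analysis without any condition: "we will count the rate of pelvic muscle strength reaching grade 4 at 6 months postpartum between EG and CG by chi-square test", with Fisher's exact test as the alternative. Section 4 lists "the occurrence of SUI" as the first secondary outcome, and Section 3 makes it a yes/no variable: "SUI is defined by SUI symptoms or a positive result of the cough stress test".

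On adjustment, Section 4.2 has one fragment, placed after repeated ANOVA at the end of the paragraph: "multivariable linear regression models if potential confounders were imbalanced". It has no verb and names no outcome. Logistic regression appears in the same section with a different job: "logistic regression analysis is used for correlation analysis".

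The article also identifies prognostic information. Section 1 says "Pregnancy and vaginal delivery have independently been proved to be the risk factors" and links them to weaker pelvic floor muscles. Section 3 says that "delivery history of pregnancy, weight gain during pregnancy, and fetal weight, would be collected at the enrollment visit of the study".

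**The concern.** Two features of the stated rule are poor choices for a randomised trial.

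**The trigger.** Under 1:1 randomisation a baseline difference carries no information about whether a covariate matters for the outcome. A modest imbalance in a strong predictor can matter more than a large one in a weak predictor, yet a test of balance picks out the second. A factor that the article itself treats as prognostic is used only when chance makes it differ.

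**The model.** The only model named for adjustment is linear regression, with no limit to quantitative outcomes. The primary endpoint and SUI are binary, and the natural model for them is assigned to another purpose.

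At stake are the precision that baseline data could supply and an avoidable choice between an unadjusted and an adjusted result that exists only in some realisations of the trial.

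**Working it through.** **1. The plan's own figure.** Section 4.1 states 90.248% power with 106 per group, control rate 0.2, and experimental rate 0.4 under the null and 0.6 under the alternative, by a one-sided unpooled Z test. SE = √((0.2×0.8 + 0.6×0.4)/106) = 0.0614. Power = Φ(0.2/0.0614 − 1.96) = 90.248%, taking one-sided alpha as 0.025. The article does not state alpha, but this value recovers its figure. No sample-size figure changes on this point.

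**2. How often the condition is met by chance.** The article gives no criterion for imbalance, so p<0.05 and independent variables are assumed.

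- Any one named factor: 5% of trials (10% if the criterion were p<0.10).
- At least one of k candidates, 1 − 0.95^k: 23% for k = 5, 40% for k = 10, 54% for k = 15, 64% for k = 20.
- Section 3 lists 16 or 17 demographic and background items, depending on how physical activity is counted: 1 − 0.95^16 = 56% and 1 − 0.95^17 = 58%. These are upper illustrations. Not every item need count as a potential confounder, and several (height, weight, BMI, prenatal maximum weight, weight gain) are related.

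**3. Precision forgone.** The article gives no covariate effect sizes, so a range is shown. For a covariate explaining a share R² of outcome variance, adjustment shortens the confidence interval by about 1 − √(1 − R²) and is worth a sample 1/(1 − R²) times as large.

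| R² (assumed) | CI shorter by | Equivalent sample |
|---|---|---|
| 0.10 | 5% | ×1.11 |
| 0.20 | 11% | ×1.25 |
| 0.30 | 16% | ×1.43 |

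For scale, a factor split 50:50 with success 20% versus 60% has R² = 0.25×0.4²/(0.4×0.6) = 0.167. Under the rule, any such gain is available in about 1 trial in 20 for a given factor.

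**4. Simulation of the rule.** Assumptions: 10,000 trials, 106 per arm, 10 independent covariates of which 3 are prognostic (log-odds 0.8 per SD), imbalance at p<0.05, and a linear model on the 0/1 outcome.

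| Analysis | Type I error | Power (rates about 22% vs 37%) |
|---|---|---|
| Unadjusted | 5.1% | 70.0% |
| Adjust if imbalanced | 4.5% | 70.3% |
| Three covariates fixed in advance | 4.7% | 80.3% |
| Either unadjusted or triggered result claimed | 5.55% | 72.3% |

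The power contrast uses a smaller effect than planned. At 20% versus 60%, a two-sided 5% test of no difference with 106 per group already has power above 99.9%. There the gain appears as a narrower interval, not as power.

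A second null set-up (104 per arm, one 20%/60% factor, 16 unrelated covariates) gave 4.3% for the rule followed as written. A separate run of that set-up gave 5.8% if either result may be claimed, against 5.2% for the unadjusted test.

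**5. What the linear model would estimate.** Fitted to the 0/1 endpoint, it gives an adjusted rate difference, which in the simulation equalled the unadjusted one (0.154 each). Fitted to the MOS grade, it gives a difference in mean grade, which does not determine the rate. As an illustration, a control group with 5/25/50/20% at grades 1/2/3/4 has mean 2.85 and rate 20%. An experimental group with 80/20% at grades 3/4 has mean 3.20 and the same rate of 20%.

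**The case against.** The strongest defence is that the primary test is not conditional at all. The fragment follows repeated ANOVA and names no outcome, so it can be read as a supplement for the quantitative outcomes (ultrasound, pelvic rotation, body composition). That reading is reasonable. A reader might infer that the primary analysis switches from a chi-square test to a linear model, with a changed estimand. The text does not say so, and the estimand changes only if MOS grade is modelled in place of the 0/1 endpoint.

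Second, the fragment speaks of potential confounders, not of all baseline variables. So it cannot be said that plainly unrelated variables would enter. This stands, but chance still decides which plausible predictors are used.

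Third, the error rate is barely touched. A reader might calculate 6.5% to 7.6% for R² of 0.10 to 0.30 by supposing that a prognostic adjusted result is always on hand to set beside the unadjusted one. The stated rule makes such a result available only occasionally, so that range does not apply; forcing the adjustment in every trial was needed to reach 7.1%.

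Fourth, the covariate list, the imbalance criterion and the ranking of the two analyses may sit in a full protocol or SAP that is not shown. Their absence is therefore not counted here. What remains is the condition and the model that the article does state.

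**Conclusion.** The point holds as a correction to a stated rule for adjustment. Making adjustment depend on observed imbalance is a poor rule under randomisation, and naming only linear regression for it, without restriction, does not suit a binary primary endpoint or SUI.

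The main cost is precision. A named prognostic factor would be used in about 5% of trials (p<0.05 criterion assumed), and in the simulation the rule added almost nothing over no adjustment, while covariates fixed in advance added about 10 percentage points of power at a smaller effect than planned. Type I error is not materially inflated: about 4.5% if the rule is followed, and about 5.5% if either result may be claimed, against about 5% unadjusted. These sizes rest on assumed covariate effects, independence and the p<0.05 criterion.

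The unconditional chi-square or Fisher test and the sample size stand. The change should be made, but the primary conclusion does not depend on it.

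**What to change.** In Section 4.2:

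- Delete the condition on imbalance.
- Name a short set of prognostic covariates now, from data already collected or known at enrolment (for example mode of delivery, parity and weeks postpartum), and use them whatever the observed balance.
- For the grade 4 rate and SUI, use logistic regression standardised to a rate difference with a 95% confidence interval. Keep linear regression for quantitative outcomes.
- State whether the chi-square/Fisher test or the prespecified adjusted analysis is decisive, and report the other as a sensitivity analysis.

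This costs one or two sentences and needs no new data or participants. The small downside is that covariates must be chosen before baseline data are seen and a few degrees of freedom are used.
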